## Abstract

**Background:** Following an acute ischemic stroke (AIS), rapidly initiated reperfusion therapies [i. e., intravenous thrombolysis (IVT) and endovascular treatment (EVT)] demonstrate robust clinical efficacy. However, only a subset of these patients can benefit from these therapies due to their short treatment windows and potential complications. In addition, many patients despite successful reperfusion still have unfavorable outcomes. Thus, neuroprotection strategies are urgently needed for AIS patients. Chlorpromazine and promethazine (C+P) have been employed in clinical practice for antipsychotic and sedative purposes. A clinical study has also shown a neuroprotective effect of C+P on patients with cerebral hemorrhage and subarachnoid hemorrhage. The safety, feasibility, and preliminary efficacy of intravenous administration of C+P in AIS patients within 24 h of onset will be elucidated.

**Methods:** A prospective randomized controlled trial is proposed with AIS patients. Participants will be randomly allocated to an intervention group and a control group with a 1:1 ratio (*n* = 30) and will be treated with standard therapies according to the current stroke guidelines. Participants allocated to the intervention group will receive intravenous administration of C+P (chlorpromazine 50 mg and promethazine 50 mg) within 24 h of symptom onset. The primary outcome is safety (mainly hypotension), while the secondary outcomes include changes in functional outcome and infarction volume.

**Discussions:** This study on Rapid Intervention of Chlorpromazine and Promethazine for Hibernation-like Effect in Stroke (RICHES) will be the first prospective randomized controlled trial to ascertain the safety, feasibility, and preliminary efficacy of intravenous C+P as a neuroprotection strategy in AIS patients. These results will provide parameters for future studies, provide insights into treatment effects, and neuroprotection with phenothiazine in AIS.

**Clinical Trial Registration:**
www.chictr.org.cn, identifier: ChiCTR2000038727.

## Introduction

Due to its high rate of mortality and morbidity, ischemic stroke is a devastating public health concern which also results in a high socioeconomic burden (1, 2). Intravenous thrombolysis with recombinant tissue plasminogen activator (rt-PA) is an important method for the treatment of acute ischemic stroke. However, due to the narrow time window, disparate national health awareness, uneven distribution of medical resources, traffic congestion, and potential complications, only around 2.4% of patients receive this treatment currently in China (3). The mortality at 3–6 months after intravenous thrombolysis was not significantly reduced, and is as high as 17.9%, with 2/3 of the patients having varying degrees of disability (3–5). Therefore, attention must be given to both vascular recanalization and neuroprotection. Exploring fast and effective neuroprotection strategies to save time for recanalization strategies and improve prognosis will become a key strategy in the treatment of AIS. We believe chlorpromazine and promethazine (C+P) may benefit patients in the acute setting of AIS.

Hibernation is an altered physiological state during times of food shortage and is characterized by drastic decreases in both body temperature and metabolic rate. Animals in hibernation withstand the decline of cerebral blood flow without experiencing brain damage (6, 7). In acute ischemic stroke, the cascade reaction caused by ischemia leads to irreversible damage to the brain within minutes (8). If a hibernation-like state can be induced in AIS patients, it may reduce brain metabolism allowing the patient to reach a balance point between energy supply and demand. This may increase tolerance to ischemia and hypoxia. C+P are the two most widely used phenothiazine drugs to induce hibernation (9). C+P are both FDA-approved and routinely used in severe brain injury, brain edema, central high fever with restlessness, mental illness and delirium (9, 10). Existing data reveal that C+P is safe for most patients (11, 12). A previous clinical study found that a mixture of drugs, including chlorpromazine 50 mg + promethazine 50 mg + dolantin (pethidine) 100 mg, named as “lytic cocktail” was injected intravenously to produce sedation, analgesia, amnesia, hypotension, hypothermia, and blockade of the functions of the sympathetic and parasympathetic nervous systems during an event (9). The drugs reduced the mortality and neurological deficit of patients with acute cerebral hemorrhage and subarachnoid hemorrhage (13). Although a neuroprotective role was not investigated in acute ischemic stroke, the safety of an oral C+P regimen has been demonstrated by our group in stroke patients (14). In addition, our previous studies have demonstrated a neuroprotective effect of C+P in rat ischemic stroke models (15). The neuroprotective effect was due to the reduction in reactive oxygen species (ROS)-mediated oxidative injury (15), brain inflammation (16), apoptosis (17), and reduction in blood-brain barrier (BBB) dysfunction after ischemic stroke (18). Importantly, this neuroprotection was not completely dependent upon the reduction of body temperature. As a safe, effective, cost-efficient “old drug,” C+P may be repurposed as a promising new therapy to achieve neuroprotection in AIS patients. We thus designed this single-center, prospective randomized controlled study on Rapid Intervention of Chlorpromazine and Promethazine for Hibernation-like Effect in Stroke (RICHES) to verify the safety, feasibility, and preliminary efficacy of immediate intravenous administration of C+P at a dose as previously reported for AIS.

## Methods

### Study Design

This is a single-center, prospective randomized controlled trial. It will be performed in patients with acute ischemic stroke (AIS) onset within 24 h. Participants meeting inclusion criteria but not exclusion criteria will be randomly allocated to the C+P or the control group whether they received IVT or not. Participants allocated to the intervention group will receive intravenous administration of C+P within 24 h of symptom onset, within the first 60 min of administration. C+P will be administered after rt-PA if the patients received IVT. Seeing that early mechanical thrombectomy has an absolute difference in the rate of functional independence, as compared with alteplase alone (19, 20), this study will not include patients treated with EVT. *Via* the medical records, the demographic information, chronic medical history (diabetes, hypertension, hyperlipidemia, coronary heart disease), smoking history, alcohol drinking history, and NIHSS score at admission will be collected. Magnetic resonance imaging (MRI) will be performed at baseline and on days 3 and 90. NIHSS and mRS will be evaluated at baseline and immediately after administration, and on days 2, 3, 7, 14, and 90. All participants or proxies will be informed of potential risks and possible benefits and consented for this study. The consent will be provided to a legal representative if the patients do not have the capacity to consent. This study was approved by the ethics committee of Luhe Hospital, Capital Medical University, Beijing, China and has been registered at www.chictr.org.cn with ChiCTR2000038727. An independent physician will monitor the health and safety of the participants.

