### Randomization and Blindness

During the recruitment period, participants will be allocated 1:1 to two groups (*n* = 30) by computer-generated randomization procedures using opaque envelopes. A research assistant not involved in the study will prepare the envelopes before the study. After recording baselines measures, participants will be randomly allocated to either the intervention or the control group by the treating physicians who will open the sealed opaque envelopes. In order to minimize selection bias, patients and assessors involved in the trial will be masked to treatment allocation. All outcome measurements will be assessed by two observers blinded to the treatment plan, any disagreement will be resolved by reaching a consensus between the two. If no consensus can be reached, a third observer blinded to the treatment assignment and not involved in the clinical treatment plan will have a final decision. Finally, an independent investigator blinded to the treatment assignment will collect the data of outcomes and information of the group, and analyze them.

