### Estimation of Sample Size

There is no data available for reference because no completed clinical study of C+P in AIS patients without EVT currently exists. However, Hertzog has suggested that 10 to 20 patients in each group are sufficient to assess the feasibility of a pilot study (22) while Dobkin has shown that 15 patients in each group is usually enough to decide whether a larger multicenter trial should be conducted (23). Therefore, our goal is to recruit 15 patients in each group, a similar number of samples was selected for another protocol (24). The results of this study should be able to determine the initial safety and feasibility of intravenous infusion of C+P in AIS patients. The data will be used to estimate sample size and conduct a power calculation to plan a phase-2 trial for efficacy.

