C+P, as the main component of the classic prescription “lytic cocktail,” are the two most studied phenothiazine drugs (9). Based on their sedative and antipsychotic effects, they are widely used in severe brain injury, brain edema and schizophrenia since the 1950s (10). Existing data have demonstrated their clinical safety (11, 12). Chlorpromazine has been shown to protect against ischemic injury in liver, kidney, spinal cord and brain (33–39), promethazine can reduce the oxygen consumption and basic metabolic rate of the brain and whole body, as well as improve the tolerance of a tissue to hypoxia (40). In our animal studies, C+P has been found to reduce infarct volumes (from 50.3 to 35.7%, *p* < 0.05) and neurological deficits (from score 3.5 to 2.8, *p* < 0.05) in 2 h middle cerebral artery occlusion models. This appears most likely independent of drug-induced systemic hypothermia (15). In clinical practice, as mentioned above, oral administration of C+P after AIS was safe and there were no adverse reactions (14). Therefore, C+P application in stroke seems to have several advantages, such as simple implementation, rapid onset, cost-efficient, minimal known serious side effects in a small study. In addition, it could ultimately be administered in the field prior to reperfusion for neuroprotection and time window extension.

There are limitations to this study. First, this is a single-center, small sample experiment, which may affect the generalizability of the interventions and opens the study up to spurious results. Second, the target dosage has been shown to be safe and reliable in other small cohort experiments, but the dose used in the present study may still need optimization. In addition, there is a concern that an intravenous administration of an equal dosage might have more interactions given better bioavailability. The current study protocol will not include AIS patients who receive EVT to avoid interactions between C+P and moderate sedation or general anesthesia.

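### IVT status plays no described part in the 15 v 15 allocation, the listed baseline data or the named tests, so a chance IVT imbalance could modestly bias the 90-day comparison

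*Protocol article*

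**What the plan says.** Study Design states that eligible patients "will be randomly allocated to the C+P or the control group whether they received IVT or not", and that where IVT is given the study drug follows it. Randomization and Blindness says "participants will be allocated 1:1 to two groups (*n* = 30) by computer-generated randomization procedures using opaque envelopes"; it names no stratification factor and no blocks. Estimation of Sample Size fixes the numbers: "our goal is to recruit 15 patients in each group".

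The baseline data listed in Study Design are demographics, chronic medical history, smoking, alcohol and admission NIHSS. IVT is not on the list. Statistical Analyses names the chi-square test, Fisher's exact test, a continuity correction, the t-test and the Mann-Whitney test. All are comparisons of two groups without a covariate or stratum.

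On reperfusion itself, the Abstract says that IVT and endovascular treatment (EVT) "demonstrate robust clinical efficacy". Study Design leaves out EVT patients because "early mechanical thrombectomy has an absolute difference in the rate of functional independence, as compared with alteplase alone". The limitations paragraph of the Discussion adds a second reason: the study "will not include AIS patients who receive EVT to avoid interactions between C+P and moderate sedation or general anesthesia".

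**The concern.** The article regards IVT as an effective treatment and deliberately admits patients with and without it, yet describes no step that balances IVT, tabulates it or allows for it. In 30 patients, randomisation cannot be relied on to balance a binary prognostic factor.

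An excess of IVT patients in one arm would pull NIHSS, infarct volume and 90-day mRS in a common direction, and the named tests would not remove the pull. Two decisions depend on those comparisons. The move to phase 2 requires, among other things, no difference in 90-day prognosis between the arms, and the pilot data are to be used for the phase-2 sample size. A chance imbalance could mimic a difference or hide one. With IVT absent from the listed baseline data, a reader of the results might be unable to tell.

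**Working it through.** **Plan's own figure.** The sample size rests on pilot-study rules of thumb, with no power, effect size or event rate, so no formula can reproduce it. The arithmetic agrees: 2 × 15 = 30.

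**Inputs.**
- Patients per arm: 15 (Estimation of Sample Size).
- IVT share q: not given for the centre. The Introduction's only figure is national: "only around 2.4% of patients receive this treatment currently in China". I therefore use 2.4% and an assumed range of 10% to 50%.
- IVT effect on mRS 0–2: not given; assumed 10 to 20 points, with 30 as an extreme.
- Good outcome without IVT: assumed 33%.

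**Step 1: chance of imbalance.** Without stratification, the IVT counts in the two arms are independent Binomial(15, q). The exact chance that they differ by at least 3 or at least 4 patients is:

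| IVT share | Expected IVT patients (30 × q) | Differ by ≥3 | Differ by ≥4 |
|---|---|---|---|
| 2.4% | 0.72 | 0.7% | 0.05% |
| 10% | 3 | 12% | 3% |
| 20% | 6 | 25% | 11% |
| 30% | 9 | 32% | 16% |
| 40% | 12 | 35% | 19% |
| 50% | 15 | 36% | 20% |

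With the number of IVT patients among the 30 held fixed (hypergeometric), a difference of 4 or more has probability 17% for 6 IVT patients, 25% for 10 and 26% for 12.

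**Step 2: shift in the contrast.** Shift = (difference in IVT patients ÷ 15) × IVT effect.
- 4 patients, 10 points: 4/15 × 10 = 2.7 points.
- 4 patients, 20 points: 4/15 × 20 = 5.3 points.
- Extreme, 6 patients and 30 points: 6/15 × 30 = 12 points. At a 50% share, a difference of 6 or more occurs in about 4% of trials.

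**Step 3: compare with sampling error.** The standard error of a difference in proportions with 15 per arm is √(2p(1−p)/15). At p = 0.33 it is 17.2 points; at p = 0.50 it is 18.3 points. A shift of 2.7 to 5.3 points is roughly 0.15 to 0.3 standard errors.

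**Step 4: type I error.** No drug effect, 10 IVT patients of 30, 33% good outcome without IVT, 5% level taken as two-sided, exact enumeration:

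| IVT effect | IVT split | Chi-square | Fisher |
|---|---|---|---|
| 20 points | averaged over all splits | 4.9% | 1.6% |
| 20 points | 5/5 | 4.5% | 1.4% |
| 20 points | 7/3 | 5.5% | 1.9% |
| 20 points | 8/2 | 6.7% | 2.5% |
| 30 points | averaged over all splits | 4.7% | 1.6% |
| 30 points | 8/2 | 8.7% | 3.5% |

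Averaged over splits, the error rate stays below 5%. It rises only given a bad split, and then slightly.

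**Step 5: what stratification would change.** With permuted blocks of at most 4 within each IVT stratum, the arms can differ by at most 2 IVT patients. The largest shift at a 20-point effect is then 2/15 × 20 = 2.7 points.

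**The case against.** The strongest reply is that stratification is absent only by silence. The article says allocation is made "by computer-generated randomization procedures using opaque envelopes", which neither affirms nor denies strata or blocks, and a journal article often leaves such detail to the full protocol. That stands, and the fix is conditional on it. What does not rest on silence alone is the explicit decision to pool, next to a list of baseline data without IVT and a list of tests without covariates. Strata cannot be added once envelopes are in use, so the question is worth settling early.

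Several stronger readings are tempting, and the documents do not support them:
- **That an IVT imbalance could pass for a drug effect on blood pressure.** Hypotension is the main safety outcome, but nothing in the article links IVT to hypotension. The point does not reach the primary outcome.
- **That the plan contradicts itself by excluding EVT as outcome-changing while admitting IVT.** The Discussion gives a second reason for excluding EVT, and the Study Design contrast is EVT against alteplase alone, not IVT against none. The two choices can coexist.
- **That the trial's false-positive rate is inflated.** Step 4 shows otherwise. Chance imbalance is already part of the randomisation distribution.

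It is also fair to say that the IVT share and effect are assumed, that at 2.4% the matter vanishes, and that NIHSS and onset time are left to chance too. Two things suggest that IVT patients are expected: recruitment is at a stroke centre, and the protocol sets an order for rt-PA and study drug. IVT is also a treatment that the article itself calls effective. The Discussion concedes that the small sample may give spurious results, but it does not mention IVT.

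**Conclusion.** The point holds in a limited form. IVT status is not used in the described allocation, the listed baseline data or the named tests. If the IVT share is 20% to 50%, roughly one trial in nine to one in five would have arms differing by 4 or more IVT patients. Given such a split and an IVT effect of 10 to 20 points, the 90-day mRS contrast is off by about 3 to 5 points.

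That is small beside a standard error of 17 to 18 points and would rarely produce a significant result alone. It matters because the estimate feeds the go rule and the phase-2 sample size, and because the remedy costs almost nothing. The size depends on the assumed share and effect, and on the full protocol not already stratifying by IVT.

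**What to change.** 1. Add IVT (yes/no) to the baseline data in Study Design and report it by arm.
2. Unless the full protocol already does so, prepare two envelope sets, IVT yes and IVT no, each 1:1 in permuted blocks of varying size (2 and 4). Keep the block sizes concealed, and state that the envelope is opened after the IVT decision.
3. In Statistical Analyses, include IVT as a covariate for NIHSS and infarct volume, and as a stratum in a supportive analysis of mRS 0–2. No stratified hypotension analysis is needed.

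**Cost.** A second stack of envelopes and about one sentence in each of three sections; no extra patients or staff. There are three downsides:
- Short blocks are somewhat predictable to the treating physicians who open the envelopes. Concealing and varying the block size limits this but does not remove it.
- Two strata, each up to 2 patients off, allow overall arm sizes as uneven as 17 v 13.
- The covariate uses one degree of freedom and gains little precision if the IVT effect is small.

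If envelopes are already in use, items 1 and 3 can still be adopted.

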### Patient Population: Inclusion and Exclusion Criteria

Participants will be recruited from the stroke center (the Stroke Intervention and Translational Center, SITC) in Beijing Luhe Hospital. The inclusion criteria are (1) ≥18 and ≤80 years old; (2) clinical diagnosis of AIS; (3) NIHSS score ≥6 and ≤25; (4) patients with time from onset to treatment ≤24 hours that did not receive endovascular treatment (EVT); (5) pre-stroke mRS ≤2; (6) informed consent provided by participant or legally authorized representative.

Exclusion criteria are as follows: (1) rapid and spontaneous relief of symptoms: NIHSS score reduced to <6; (2) hemodynamic instability, including low systolic blood pressure (SBP) and SBP ≤100 mmHg despite standard treatment; (3) medical history of Parkinson's disease, Parkinson's syndrome, neuroleptic malignant syndrome, basal ganglia disease and epilepsy; (4) allergy to phenothiazines; (5) acute myocardial infarction, acute cardiac insufficiency and/or serious arrhythmia; (6) participant in another ongoing clinical trial; (7) life expectancy of fewer than 1 year due to comorbidities; (8) any condition which the investigator judges to increase the risk of injury to the patient.

### Randomization and Blindness

During the recruitment period, participants will be allocated 1:1 to two groups (*n* = 30) by computer-generated randomization procedures using opaque envelopes. A research assistant not involved in the study will prepare the envelopes before the study. After recording baselines measures, participants will be randomly allocated to either the intervention or the control group by the treating physicians who will open the sealed opaque envelopes. In order to minimize selection bias, patients and assessors involved in the trial will be masked to treatment allocation. All outcome measurements will be assessed by two observers blinded to the treatment plan, any disagreement will be resolved by reaching a consensus between the two. If no consensus can be reached, a third observer blinded to the treatment assignment and not involved in the clinical treatment plan will have a final decision. Finally, an independent investigator blinded to the treatment assignment will collect the data of outcomes and information of the group, and analyze them.

### Interventions

Participants in both groups will receive the standard management according to the guidelines for the treatment of ischemic stroke, including blood pressure control, treatment of hyperglycemia and hyperlipidemia, antiplatelet or anticoagulation, and neurotrophic treatment (21). The body temperature of both groups will be maintained at 36.0–37.3°C. The room temperature will be 20–25°C. In order to ensure the stability of administration speed and the stability of blood pressure, patients allocated to the C+P group will undergo intravenous infusion of chlorpromazine 50 mg and promethazine 50 mg at 5 mg/h. For the choice of drug dosage, we referred to the hibernation mixture (chlorpromazine 50 mg + promethazine 50 mg) (13). Based on clinical experiences, this dose is safe and effective. The same total dose of C+P (25 + 25 mg, twice a day) given to patients has been proven to be safe in our previous study. In addition, as compared to oral administration, the current protocol with continuous small dose injection at 5 mg/h *via* a micropump will maintain a stable blood concentration. The speed will be adjusted according to the patient's reaction. This administration will keep the patient in light sedation that can be awakened and allow for physical examination at any time. The control group will receive the same dosage of normal saline at 5 mg/h. During this period, vital signs (i.e., blood pressure, heart rate, body temperature, respiratory rate of the patients), changes in consciousness, and possible adverse drug reactions will be closely monitored. If the patients show a tendency to develop adverse reactions and complications, the trial shall be stopped immediately, and routine treatment shall be given.

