### Outcomes

#### Primary Outcomes (Safety Assessment)

The main safety parameter is the incidence of hypotension requiring clinical intervention (≤90/60 mmHg). The secondary safety outcomes are the occurrence of adverse events including (1) neurologic deterioration defined as an increase of four or more points in the NIHSS within 7 days without clear explanation; (2) death during the study period regardless of cause; (3) body temperature down to below 36°C; (4) severe arrhythmias, such as sick sinus syndrome, rapid atrial fibrillation, supraventricular tachycardia, etc., which may cause palpitations, chest tightness, dizziness and other clinical manifestations; (5) liver damage: alanine aminotransferase (ALT) and aspartate aminotransferase (AST) concentrations were doubled; (6) seizures: epilepsy occurs within 2 weeks of stroke; (7) extrapyramidal responses (tremor, rigidity, salivation, and bradykinesia).

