### Statistical Analyses

The endpoint event analysis is based on the intention-to-treat (ITT) principle, including all randomly enrolled subjects. If compared to the control group, the treatment group did not have an increase in the incidence of adverse reactions and there was no difference in 90 days prognosis between the two groups, we would move forward with a phase-2 trial.

Categorical variables including the proportion of good functional outcomes and the frequency of adverse events will be presented as counts and percentages. χ^2^-test, Fisher exact-test, or continuity correction will be used where appropriate for comparison between the two groups. If the continuous variables including NIHSS score and infarct volume conform to the normal distribution, it shall be indicated by mean ± standard, and tested by *t*-test, and if it does not conform to the normal distribution, it shall be indicated by median and interquartile range and tested by Mann-Whitney *U*-test. *p* < 0.05 will be considered statistically significant. SPSS 22.0 software will be used for statistical analysis.

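### The stopping sentence acts on a mere tendency to adverse reactions, leaves open what is stopped, and no listed outcome counts the stops, so the safety comparison may lean towards safe

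*Protocol article*

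**What the plan says.** All places are in the protocol article.

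- **Interventions.** Chlorpromazine and promethazine (C+P) are infused by micropump and the control group receives saline. During this period vital signs, "changes in consciousness, and possible adverse drug reactions will be closely monitored". Short of stopping, "The speed will be adjusted according to the patient's reaction". The section ends: "If the patients show a tendency to develop adverse reactions and complications, the trial shall be stopped immediately, and routine treatment shall be given".
- **Primary Outcomes (Safety Assessment).** "The main safety parameter is the incidence of hypotension requiring clinical intervention (≤90/60 mmHg"). Secondary safety events are neurologic deterioration within 7 days, death, low body temperature, severe arrhythmia, liver damage, seizures within 2 weeks and extrapyramidal responses. Death is counted as "death during the study period regardless of cause".
- **Study Design.** "NIHSS and mRS will be evaluated at baseline and immediately after administration, and on days 2, 3, 7, 14, and 90". MRI is at baseline and days 3 and 90.
- **Statistical Analyses.** "The endpoint event analysis is based on the intention-to-treat (ITT) principle, including all randomly enrolled subjects". A phase-2 trial follows if adverse reactions are not more frequent under treatment and 90-day prognosis does not differ. The last paragraph of the Discussion puts the safety condition as no significant difference in drug-related adverse events.
- **Randomization and Blindness.** Treating physicians open the envelopes. Patients and assessors are the ones described as masked.

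**The concern.** Safety is the primary question, and the go decision rests on comparing event frequencies between two groups of 15. The stopping sentence bears on that comparison in two ways.

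First, its object is the trial. The article does not say whether this means the infusion, the patient's participation or the study. Two of these three meanings would leave scheduled assessments undone.

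Second, its trigger lies upstream of the endpoint. A patient whose blood pressure is falling can be stopped for a tendency and then never reach ≤90/60 mmHg with intervention. That patient is scored as event-free although the regimen could not be completed. No listed outcome records the stop, although feasibility is one of the stated aims. Events averted by stopping the active drug would fall mainly in the C+P arm, because stopping saline can be expected to avert little. The error would then favour C+P. The trigger is also a matter of judgement. If the physicians who opened the envelopes make it, the sentence may be applied differently in the two arms, and blinded assessment afterwards cannot recover an event that was pre-empted.

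**Working it through.** **1. What is stopped: three readings set against the rest of the plan.**

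- *The patient's infusion stops.* This fits follow-up to day 90 and intention-to-treat. The context supports it: the sentence follows infusion speed and monitoring during the infusion, and its consequence is routine treatment for the patient.
- *The patient's participation ends.* The remaining NIHSS, mRS and MRI assessments could not be completed, and the analysis of all randomised patients would lack data.
- *The study ends.* This fits neither the recruitment goal ("our goal is to recruit 15 patients in each group") nor follow-up of those already enrolled.

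**2. Trigger against endpoint.** The trigger is a tendency to a reaction. The main endpoint is a blood pressure at or below a threshold that also requires intervention. The first can occur without the second, and acting on the first can prevent the second. This holds on all three readings.

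**3. Where a stop would be counted.** The primary and secondary outcome lists cover hypotension, seven types of adverse event, mRS, infarct volume and NIHSS. None is an early stop or a rate reduction.

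**4. Size.** The plan's only related figure is the sample size: 2 × 15 = 30, which agrees with n = 30 read as the total. The plan gives no event rates, so the counts below are assumptions. The significance level is 0.05 as stated; two-sided testing is assumed. With few events the expected counts are below 5 (for 5 events in 30 patients, 2.5 per arm), so Fisher's exact test is the applicable one of those listed.

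For k events in 15 C+P patients and 0 in 15 controls, the two-sided value is p = 2 × C(15,k) / C(30,k):

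| Counted in C+P | Rate | Calculation | p |
|---|---|---|---|
| 5/15 (none pre-empted) | 33.3% | 2 × 3003 / 142506 | 0.042 |
| 4/15 (one pre-empted) | 26.7% | 2 × 1365 / 27405 | 0.100 |
| 3/15 (two pre-empted) | 20.0% | 2 × 455 / 4060 | 0.224 |

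Every patient is retained and analysed as randomised in all three rows. One pre-empted event moves the comparison across 0.05.

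**5. Range.** This is the probability that Fisher's test reaches p < 0.05 with 15 per arm and a true control risk of 5%. The last column assumes that half of the C+P events are pre-empted and none in control:

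| True C+P risk | No pre-emption | Half pre-empted |
|---|---|---|
| 20% | 0.083 | 0.006 |
| 30% | 0.275 | 0.030 |
| 40% | 0.519 | 0.083 |

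Power is low even without pre-emption, so pre-emption adds to an existing weakness.

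**The case against.** The strongest reply is that the sentence is loosely worded but harmless. In context it ends one patient's infusion, and intention-to-treat exists to keep such patients in the analysis. This stands. A reader might infer that the sentence contradicts intention-to-treat, removes the patients who carry the safety signal, or makes the stated analysis impossible. The documents do not support that. No text withdraws, replaces or excludes a stopped patient, Statistical Analyses keeps everyone randomised, and the visit schedule makes no exception for stopped patients. A contrast such as 3/15 against 0/12 arises only by dropping patients whom the plan says to keep, so it does not measure this problem.

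A second reply is that the go rule in Statistical Analyses speaks of adverse reactions in general, and that reactions are closely monitored, so a reaction prompting a stop may well be recorded. This stands in part. Nothing says that it goes unrecorded, but nothing makes a tendency that was halted count as a reaction, and the main endpoint has a threshold that such a patient may not meet.

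Third, several safety outcomes run well beyond the infusion (7 days, 2 weeks, the whole study), so stopping does not prevent their being observed. That is right, and it confines the pre-emption chiefly to events during the infusion, hypotension above all. One may add that a lower hypotension count under early stopping is the true safety of the regimen as managed. That is a legitimate quantity, but it can be interpreted only if the number of patients who could not complete the regimen is reported beside it.

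Finally, a condensed article may leave the definition of tendency to the full protocol. Agreed; its absence is not the point here.

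**Conclusion.** The point holds as an ambiguity with a possible bias. It is not a demonstrated contradiction or exclusion. The object of the stop is unclear, and two of its three readings would not fit follow-up to day 90 or the stated analysis. On every reading, the stop can pre-empt the main safety endpoint and is not counted among the listed outcomes, so the comparison behind the go decision may lean towards safe even with complete follow-up.

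With 15 per arm and 0/15 in control, a single pre-empted event can change p from 0.042 to 0.100, and two give 0.224. These counts are assumed, as are two-sided testing and pre-emption confined to the C+P arm. The p-values bear on the Discussion's condition of no significant difference. The condition in Statistical Analyses does not mention significance, and there the effect is on the raw incidence: 33.3% falls to 26.7% and then 20.0%. That treating physicians would call the stop is likely but not stated. This is a cheap improvement.

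**What to change.** Reconcile Interventions, Primary Outcomes and Statistical Analyses:

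1. State whether the infusion, the patient's participation or the study is stopped.
2. State that every randomised patient, stopped or not, stays in all scheduled safety, NIHSS, mRS and MRI assessments to day 90 and is analysed as randomised.
3. Add early stop or rate reduction for a reaction, with the reason and the dose delivered, as a tolerability and feasibility outcome reported by arm.
4. Include stops for a listed reaction in the go decision, next to the counted adverse events.

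No clinical stopping threshold is proposed; that choice remains with the sponsor. The cost is protocol wording and one case-report field, since the visits are already scheduled. The downside is a possibly less favourable safety figure.
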